### Data analysis

Baseline demographics of the study population will be analysed using descriptive statistics.

#### Relationship between time spent walking and outcome

Multivariable logistic regression analysis will be used to investigate the relationship between the time spent walking in the first week after surgery and outcome at six months using SPSS software. The dependent variable in the logistic regression model will be the change in score on the ODQ, SF-36 (PCS), NRPS (back) and NRPS (leg) between baseline and six months. The change in scores on the ODQ, SF-36 (PCS) and NRPS will be dichotomised based on the threshold required to demonstrate a substantial clinical benefit.

Thresholds required to meet the minimum clinically important difference (MCID) have been identified for the ODQ, the SF-36 (PCS) and the NPRS [41] (Table 2). In addition, thresholds required to obtain a substantial clinical benefit (SCB), where patients report a major improvement in symptoms, have been defined for the ODQ, SF-36 (PCS) and NRPS in the lumbar fusion population [42] (Table 2). For the purpose of this study it has been assumed that SCB following lumbar fusion surgery provides a fair estimate of substantial clinical benefit following lumbar surgery in general. These thresholds allow the change in scores to be categorised as minimal improvement (below MCID threshold), moderate improvement (above MCID threshold, below SCB threshold) and substantial improvement (SCB threshold or greater).

**Table 2 Tab2:** MCID and SCB thresholds

Outcome measurement tool	MCID (points change)	SCB (points change)
ODQ	10	18.8
SF-36 (PCS)	4.9	6.2
NPRS (back)	2	2.5
NRPS (leg)	2	2.5

As all participants in this study are undergoing surgery with the aim of improving pain and physical function, it expected that the majority of participants in this study will report an improvement in scores above the MCID threshold. Therefore the SCB threshold will be used to analyse the impact of walking time on outcome (minimal/moderate improvement compared to substantial improvement). For each of the four dependent variables a multivariable logistic regression model will be generated comparing participant outcome relative to the SCB threshold.

With the exception of pre-operative function and surgical procedure, all confounding variables will be dichotomised (Table 3).

**Table 3 Tab3:** List of independent variables and classification for statistical analysis

	Classification				
1. Post-operative activity	Time spent walking (minutes)				
2. Age	1. < 65 years	2. ≥ 65 years			
3. Gender	1. Male	2. Female			
4. Current smoking status	1. Non-smoker	2. Smoker			
5. Obesity	1. BMI < 30	2. BMI ≥ 30			
6. Diabetes	1. Not diabetic	2. Diabetic			
7. Depression	1. PHQ-9 < 10	2. PHQ-9 ≥ 10			
8. Anxiety	1. GAD-7 < 10	2. GAD-7 ≥ 10			
9. Duration of pain/symptoms	1. < median (months)	2. ≥ median (months)			
10. Neurological deficit	1. No deficit	2. Neurological deficit			
11. Pre-operative activity	1. IPAQ-SF - Mod/high	2. IPAQ-SF - low			
12. Pre-operative mobility	1. ODQ (section 4) < 3	2. ODQ (section 4) ≥ 3			
13. Surgical procedure	1. Decompression	2. Disc surgery	3. Fusion		
14. Multi-level surgery	1. Single level surgery	2. Multi-level surgery			
15. Preoperative function (ODQ%)	1. 0–20	2. 21–40	3. 41–60	4. 61–80	5. 81–100

Bivariate analyses will be carried out to assess the association between each confounding variable and each outcome measure. The variables that have an independent association with outcome will be included in the final regression model. Analysis of correlation between the independent variables will be carried out to assess for multicollinearity. Where variables are highly correlated, either the more relevant variable or the variable with the more complete data set will be retained in the final regression model [43].

Missing independent variable data will be managed based on the quantity of missing data per participant and per variable. In the case of missing or incomplete accelerometry data, participants will be removed from analysis where three or more days of recordings are missing. In the case of one to two days of missing data, the time spent walking each day will be estimated based on the mean daily walking time of the total sample population. Comparisons will be made between the characteristics of participants with and without missing data to ensure minimisation of bias [43]. The underlying assumptions of the model will be assessed using the SPSS software “goodness of fit” testing.

Bivariate analysis will be used to examine the association between post-operative walking time, and both patient satisfaction and post-operative complications as reported at six months.

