### Outcome measures

An outcome assessment timeline and summary of assessment tools used is provided in Table 1.

**Table 1 Tab1:** Timeline of outcome assessment

Pre-operative (baseline)	
Baseline demographics:	Age, sex, smoking status, height, weight, diabetic history
History of back/leg symptoms:	Duration of symptoms, neurological deficit
Physical function:	ODQ, SF-36
Pain:	Back and leg pain (NRPS)
Physical activity:	IPAQ-SF
Psychological status:	Depression (PHQ-9), anxiety (GAD-7)
Post-operative (days 1–7):	
Surgical procedure:	Decompression, discectomy, fusion; single or multi-level
Accelerometry:	Time spent walking, step count, time spent in sedentary and active postures, number of walks
Pain:	Back, leg and wound pain (NRPS)
Supervised walking:	Patient/physiotherapist reported
Post-operative complications:	Complications requiring medical intervention and/or limit walking time
Post-operative (6 months):	
Physical function:	ODQ, SF-36
Patient satisfaction:	5 point likert scale
Post-operative complications:	Complications requiring medical intervention

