#### Dependent variable

The primary dependent variable will be self-reported function. This will be measured using a Modified Oswestry Disability Questionnaire (ODQ) [30] and the physical component summary (PCS) of the SF-36 (version 2) [31, 32]. Back and leg pain intensity using the numeric pain rating scale (0–10) (NPRS) [33] will be recorded as secondary dependent variables. The ODQ, SF-36 and the NPRS are all validated and recommended for use within the back pain population [34], and are widely used in spinal surgery research. The modified ODQ substitutes kilometres for miles to estimate walking distance, and has been validated in the Australian population [30]. The relationship between post-operative walking and each of the four dependent variables will be analysed individually.

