#### Factors associated with time spent walking immediately following surgery

Additional data will be collected on a daily basis regarding post-operative back, leg and wound pain intensity (NRPS), the need for supervision while walking, and surgical/medical complications. Reported complications will include events where the participant requires medical intervention in addition to routine post-operative care, and events that limit activity (for example, symptomatic hypotension, analgesia-induced nausea). This information will be sourced from the patient, ward staff, and patient notes. In cases where participants are discharged from the inpatient facility prior to completing the monitoring period they will be asked to record this information daily, which will then be returned to the researchers with the accelerometer following the completion of the monitoring period.

At six months, participants will be asked to report on overall satisfaction with the results of the surgery, scored on a five point likert scale. They will also be asked to describe any post-operative complications experienced after the seven day monitoring period. This will include any event directly related to the surgical procedure requiring medical intervention in addition to routine follow-up care.

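### Change in back and leg pain to six months is modelled, but the assessment schedule has no six-month pain score (2 of 4 models)

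*Protocol article*

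**What the plan says.** The article treats back and leg pain as outcomes in two places.

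- **Dependent variable.** Back and leg NPRS "will be recorded as secondary dependent variables", next to the primary function measures (ODQ and SF-36 PCS). No time point is given there. The section adds: "The relationship between post-operative walking and each of the four dependent variables will be analysed individually".
- **Relationship between time spent walking and outcome.** The modelled quantity is "the change in score on the ODQ, SF-36 (PCS), NRPS (back) and NRPS (leg) between baseline and six months", dichotomised at the substantial clinical benefit (SCB) threshold. Table 2 sets that threshold at 2.5 points for back pain and 2.5 points for leg pain. The plan is then: "For each of the four dependent variables a multivariable logistic regression model will be generated comparing participant outcome relative to the SCB threshold".

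The collection side is in Outcome measures: "An outcome assessment timeline and summary of assessment tools used is provided in Table 1". In that table the pre-operative block has a pain row ("Back and leg pain (NRPS"), and the days 1–7 block has one for back, leg and wound pain. The block headed "Post-operative (6 months" has three rows: physical function (ODQ, SF-36), patient satisfaction, and complications. The section Six-month follow-up says that outcome measures will be mailed, without listing them.

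**The concern.** A change score needs a value at both ends. For the two pain outcomes, the only schedule in the article supplies the baseline value and no six-month value, while the analysis section builds two regression models on the difference.

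Six-month follow-up is by post. Whoever assembles the questionnaire from Table 1 would leave the pain scales out, and both outcomes that the article labels secondary would then have no endpoint for any participant. An analysis plan could not repair that. The missing-data rules in the article deal with independent variables, and no imputation can rebuild an outcome that nobody reported.

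**Working it through.** No figure in the article bears on this point; the sample-size calculation is not an input and does not change. The check sets each planned outcome against the schedule.

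**Inputs**
- Outcomes needing a change from baseline to six months: four (Relationship between time spent walking and outcome).
- Instruments at each time point: Table 1 (Outcome measures).
- Other text on six-month collection: Abstract, Methods; Six-month follow-up; Factors associated with time spent walking immediately following surgery.

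**Step 1. Outcomes against Table 1**

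| Modelled outcome | Pre-operative | Days 1–7 | Six months | Both ends of the change score scheduled? |
|---|---|---|---|---|
| ODQ | yes | no | yes | yes |
| SF-36 PCS | yes | no | yes | yes |
| NPRS back | yes | yes | no | no |
| NPRS leg | yes | yes | no | no |

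Scheduled at both ends: 2 of 4. Without a scheduled endpoint: 4 − 2 = 2, both of them pain outcomes.

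**Step 2. Does other text put the NPRS at six months?**
- The Abstract says that outcomes are measured before surgery and at six months, in general terms.
- Six-month follow-up refers to mailed outcome measures and names none.
- The section on factors associated with walking time says "At six months, participants will be asked to report on overall satisfaction with the results of the surgery" and adds complications. It names no pain scale, but it does not name ODQ or SF-36 at six months either, and Table 1 schedules both. Its silence on pain is therefore not evidence.

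So no text on collection names the NPRS at six months. Only the analysis section implies it. The contradiction rests on Table 1 against the analysis section and the definition of the dependent variables.

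**Step 3. Could another scheduled measurement stand in?**
- Days 1–7 pain scores are in the schedule, but a change to the first post-operative week is not the six-month change that the models specify.
- ODQ and SF-36 are collected at six months, but neither is the 0–10 NPRS. The 2.5-point threshold in Table 2 is defined on the NPRS and cannot be applied to them.

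**Step 4. Could the gap be an artefact of how the table was read?** The six-month block has its heading and three complete rows, with no sign of a gap or redaction. The other two blocks each carry their own pain row.

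**The case against.** The strongest reply is that this is a slip in a summary table and not an outcome left uncollected. The Abstract places outcome measurement at six months, the definition of the dependent variables says that back and leg pain will be recorded, the analysis section gives pain thresholds and a model for each scale, and the wording of Six-month follow-up is broad enough to include the NPRS. One absent row stands against all of that. This argument has force and makes a table omission quite plausible. It does not close the matter, because none of those places names the NPRS among the six-month instruments and the mailed pack is not shown. Either Table 1 is incomplete or two models lack an outcome, and the article does not say which.

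A second reply is that a condensed article leaves such detail to the full protocol. That would answer silence. Here the article prints a schedule that conflicts with its own analysis.

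A third reply is that the study's main question is untouched. This is correct: research question 1 concerns function, and both function measures are scheduled at both time points.

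**Conclusion.** The inconsistency is real and can be confirmed from the article alone. Two of the four planned logistic models, those for back and leg NPRS, have no six-month measurement in the schedule.

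The consequence is conditional. If the mailed pack follows Table 1, those two models have no endpoint data; if the pack already contains the NPRS, only the table is wrong. The primary ODQ and SF-36 PCS models, and the bivariate analyses of satisfaction and complications, stand in either case.

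Two stronger conclusions are tempting, and the documents do not support them. A reader might infer that six-month pain data will certainly be absent and that every secondary conclusion is lost; that would require knowing the contents of the pack. A reader might also infer that the investigators chose not to measure pain at six months; the outcome definitions and the analysis section show the opposite intention. This is an inconsistency between sections and not a design decision.

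It still deserves correction as a priority: the possible loss covers both outcomes labelled secondary, it could not be made good at the analysis stage, and the remedy costs almost nothing.

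**What to change.** 1. Check whether the six-month questionnaire pack contains the back and leg NPRS.
2. Add a row for back and leg NPRS to the six-month block of Table 1. It would also help to name the mailed instruments under Six-month follow-up.
3. If the scales are not in the pack, add them in the same form as at baseline, so that the change score compares like with like.
4. If six-month pain can no longer be collected for enough participants, remove the two pain models from the sections Dependent variable and Relationship between time spent walking and outcome, together with the pain rows of Table 2, and report the removal. The article gives no recruitment dates, so whether the collection window is still open cannot be judged from it.

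The cost is one table row and, if needed, two 0–10 items in a questionnaire that is mailed anyway. No sample-size figure and no other model changes.

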### Participants

Participants will be recruited from St Vincent’s Private Hospital, Fitzroy (SVPHF) over a six-month period. All patients aged 18 years and older undergoing surgery for the management of a disc prolapse, degenerative disc disease, lumbar spinal stenosis and/or degenerative spondylolysthesis will be invited to participate. There will be no restriction on the nature or duration of pre-operative symptoms. Patients will be excluded if they are undergoing surgery for the management of lumbar fractures or tumours, have a history of dementia or cognitive impairment or an inability to provide informed consent, or have a history of a neurological or musculoskeletal condition resulting in progressive impairment of physical function (for example, multiple sclerosis or rheumatoid arthritis). In cases where surgery includes both lumbar and thoracic vertebrae, patients will be eligible if 50 % or more of the vertebra involved are in the lumbar region.

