## Discussion

The findings from this research will assist physiotherapists to identify patients who are expected to have either very good or poor post-operative outcomes based on their activity levels immediately following surgery, and inform physiotherapists about whether increasing activity should be a focus of post-operative rehabilitation. This will help to guide patient management during the inpatient phase, by identifying patients who are at risk of poorer outcome due to limited walking time. These patients may benefit from ongoing rehabilitation and outpatient physiotherapy services. This information will also provide a foundation for further research into interventions designed to optimise post-operative activity such as patient education resources, improved monitoring and management of post-operative pain, or the provision of additional physiotherapy sessions for patients who require supervision while walking.

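### Cutting raw change at the SCB threshold costs much of the power for walking time and, in the two pain models, fixes low-baseline participants as failures with no baseline-pain adjustment

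*Protocol article*

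**What the plan says.** In the protocol article, under Relationship between time spent walking and outcome, the outcome is a change score: "The dependent variable in the logistic regression model will be the change in score on the ODQ, SF-36 (PCS), NRPS (back) and NRPS (leg"). These changes "will be dichotomised based on the threshold required to demonstrate a substantial clinical benefit". Table 2 gives the MCID first and the SCB threshold second: "SF-36 (PCS) 4.9 6.2", "NPRS (back) 2 2.5", the same pair for leg pain, and 10 and 18.8 for the ODQ. The text defines three grades of improvement and then pools the lower two against substantial improvement. Its reason is that most participants should exceed the MCID.

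Other sections bear on this:

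- **Dependent variable:** ODQ and SF-36 PCS measure the primary outcome and the two pain scores are secondary. The pain scale is given as "Back and leg pain intensity using the numeric pain rating scale (0–10) (NPRS"), so its floor is 0.
- **Participants:** "There will be no restriction on the nature or duration of pre-operative symptoms". No minimum ODQ or pain score is required for entry.
- **Table 3:** the item "15. Preoperative function (ODQ"%) has five bands, the lowest 0–20. It is the only baseline outcome score listed. Baseline back pain, leg pain and PCS are collected (Table 1) but are not covariates.
- **Text after Table 3:** a confounder enters the final model only if it is associated with outcome in a bivariate analysis.

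**The concern.** A yes/no version of a score treats a participant who just misses the threshold like one who got worse, and one who just reaches it like one who recovered fully. That lost information cannot be bought back here, because recruitment is bounded by one hospital's admissions over six months.

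A threshold on raw change also depends on where the participant starts. On a scale with a floor of 0, anyone starting closer to 0 than the threshold is a failure whatever happens. The participants counted as failures by construction are the least affected ones. If they also walk more after surgery, more walking is linked to failure for a reason unrelated to any effect of walking. Whether that reaches the walking odds ratio depends on whether the model adjusts for the baseline of the same scale. The plan allows for this with the ODQ, but not with back or leg pain.

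**Working it through.** **1. The plan's own figure.** Five events per variable and 15 variables give 75 events. The stated minimum of 150 follows if half of participants are events: 75 / 0.5 = 150. The 50% is inferred, not stated. It is also the success rate at which a cut loses least.

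**2. Information kept by the cut.** For a normal outcome cut so that a proportion p succeeds, the relative efficiency is φ(c)² / [p(1 − p)], with c = Φ⁻¹(p).

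| p | Calculation | Kept | 250 participants are worth | 150 are worth |
|---|---|---|---|---|
| 0.5 | 0.3989² / 0.25 | 64% | 159 | 95 |
| 0.4 or 0.6 | 0.3863² / 0.24 | 62% | 155 | 93 |
| 0.3 or 0.7 | 0.3477² / 0.21 | 58% | 144 | 86 |

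**3. Power.** The approximation is Φ(atanh(r)·√(n − 3) − 1.96), with r an assumed correlation between walking time and outcome. At r = 0.20 and n = 250 it is Φ(0.2027 × 15.72 − 1.96) = Φ(1.23) = 89%. With the equivalent n of 159 it is Φ(0.2027 × 12.5 − 1.96) = Φ(0.57) = 72%. For r = 0.15 the pair is 66% and 47%; for r = 0.25 it is 98% and 89%.

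Simulations of the models themselves, all inputs assumed:

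| Setting | Linear, six-month score on walking and baseline | SCB logistic |
|---|---|---|
| n = 200, residual SD 15, 58% reach SCB, 3.0 ODQ points per SD of walking | 75% | 49% |
| Same, 3.5 points | 87% | 61% |
| n = 250, baseline ODQ mean 42, SD 16, 51% reach SCB, 0.2 SD per SD of walking, ODQ in bands | 90% | 57% |

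Repeat simulations at n = 200 gave about 74–91% against 50–66%. The simulated gap exceeds the analytic one because, given baseline, the cut lies off-centre for participants who start low or high. The last row also includes the loss from banding the ODQ.

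**4. Who cannot succeed.** Success is impossible when baseline minus 0 is below the threshold.

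- Pain: baselines 0, 1 and 2. With whole-number ratings (assumed) the real requirement is a 3-point fall.
- ODQ: every baseline below 18.8. With 2-point steps (assumed), 0 to 18 cannot succeed.
- PCS: higher is better, so a low baseline blocks nothing.

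Shares under assumed normal baselines:

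- ODQ, Φ((18.8 − mean)/SD): mean 50, SD 12 gives Φ(−2.60) = 0.5%, about 1 of 250. Mean 35, SD 18 gives Φ(−0.90) = 18%, about 46 of 250.
- Pain, Φ((2.5 − mean)/SD): mean 6, SD 2.5 gives Φ(−1.40) = 8%, about 20 of 250. Mean 4, SD 3 gives Φ(−0.50) = 31%, about 77 of 250.

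**5. Bias, with no true walking effect simulated.** The nominal rejection rate is 5%.

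- ODQ model, n = 250, walking–baseline correlation −0.25: 39% with no baseline term, 5% with the ODQ bands kept, 4% for the linear model with baseline.
- Pain models adjusted for ODQ only, correlations −0.15 to −0.25: 13–25% under one set of inputs. Under another (pain mean 5, SD 2.7) they were 18–47%, with an average walking odds ratio of about 0.77 per SD at −0.25. The spread depends largely on how closely baseline ODQ is assumed to track baseline pain.
- Pain models with baseline pain added: about 6% for the SCB logistic model, 4% for the linear model.

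**The case against.** The best defence is that SCB is a reasoned clinical choice. The aim is to predict improvement, a responder definition answers that, and the plan says why it prefers SCB to MCID. Nothing here contradicts the protocol. This stands, and is why SCB should be kept as a secondary result. It does not restore the lost power.

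It is also fair that the pain-model bias comes from the absent baseline-pain term as much as from the cut, since adding that term nearly removes it. The linear model is not free of floor effects either: with scores truncated at 0, a true slope of −3 shrank to between −2.4 and −2.8 in simulation.

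A reader might infer four stronger points, which the documents do not support:

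- **That the ODQ walking odds ratio is biased too.** Baseline ODQ is a listed confounder, and because success is nearly impossible in the lowest band it very probably passes the screen. With it kept, rejection under the null is about 5%.
- **That the nearly empty 0–20 band makes the model unusable.** It had no successes in about 26–30% of simulated samples of 250. But this disturbs a nuisance coefficient, not the walking term, and no reference category is named. Dropping baselines below 18.8 hardly moved power (46.2% and 46.4% in one setting, 54.0% and 53.8% in another).
- **That the cut defeats the stated use,** "identifying patients who are at risk of poorer outcome due to limited walking time". The same Discussion also speaks of patients expected to do very well, which an SCB cut addresses directly.
- **That low baselines block success on all four outcomes.** PCS is an exception.

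**Conclusion.** The concern holds with a limited scope.

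- **Power, all four outcomes.** Under normality the cut discards at least about 36% of the outcome information. The power figures rest on assumed effects, residual SD and success rates, but the direction does not.
- **Fixed failures, ODQ and pain.** That they can occur follows from the plan's thresholds, scale floors and entry criteria. How many there will be cannot be known from the documents; 0.5–18% for ODQ and 8–31% for pain are assumed ranges.
- **Bias, the two secondary pain models.** It is downward, and conditional on less painful participants walking more, which is plausible but not documented. In the ODQ model little bias is expected provided baseline ODQ is retained, which the screening rule makes likely but does not guarantee.

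This is a weakness in the choice of primary analysis that should be changed, not an error that invalidates the study.

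**What to change.** 1. For each outcome, make the primary analysis a linear regression of the six-month score on walking time, the continuous baseline of the same scale and the confounders. The baseline term is always included and not subject to bivariate screening.
2. Keep the four SCB logistic models as secondary, with the same continuous own-baseline term (for the ODQ, in place of the five bands).
3. For ODQ and pain, report how many participants could not reach the threshold, and restrict the SCB models to those who could (baseline ODQ of at least 18.8; baseline pain of at least 3).

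This changes analysis wording only. The baseline scores are already collected. The six-month pain score is already needed for the planned change score, although Table 1 does not list it at six months, so that entry should be checked. The costs are small: the primary estimate is in points per unit of walking time rather than an odds ratio, floor effects at 0 shrink the linear slope somewhat, and the SCB models lose participants who could not have succeeded.

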#### Independent (confounding) variables

Data will be collected for variables where there is either evidence to suggest they influence outcome following lumbar spinal surgery, or there is or strong theoretical rational for their inclusion. This will include age, gender, current smoking status [14, 15], obesity [14, 18], diabetes [14, 16, 17], depression [19, 20], duration of pain/symptoms [35], neurological deficit [14], anxiety, pre-operative activity, pre-operative mobility, surgical procedure, multi-level surgery, and pre-operative function.

Depression will be assessed using the Patient Health Questionnaire Depression Scale (PHQ-9), using a cut off score of ≥10 [36]. The PHQ-9 is a short, valid and reliable measure of depression, and has been recommended for use within the chronic back pain population [37]. Anxiety will be scored using the Generalised Anxiety Disorder 7-item Scale (GAD-7), using a cut off score of ≥10 [38]. The GAD-7 is a brief, seven question scale used to screen for, and assess the severity of anxiety. It has been validated in the general population [38]. Neurological deficit will be assessed by asking the participant if he/she is aware of any changes to the sensation or strength in their affected lower limb. This level of information is deemed appropriate for this study, as any sensory or motor deficit that the participant is unaware of is unlikely to have an impact on functional ability. Pre-operative activity will be assessed using the International Physical Activity Questionnaire Short Form (IPAQ-SF) [39, 40]. The IPAQ-SF is a brief, reliable seven item questionnaire that requires participants to report on physical activity undertaken over the previous seven day period [39, 40]. Physical activity is categorised into low, moderate and high activity levels. As it is expected that the majority of participants will report either low or moderate activity levels, the two categories of low and moderate/high activity levels will be used for data analysis. Baseline ODQ score will be used as a measure of pre-operative function. Pre-operative mobility will be categorised based on the response to Section 4 (Walking) on the ODQ. Participants will be categorised as having limited mobility if they score 3 or more - unable to walk more than 500 m, require a walking aid, or are confined to bed.

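### Age, BMI, PHQ-9, GAD-7 and symptom duration are each cut in two for adjustment, which leaves a third or more of the confounding by each of them in the walking estimate

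*Protocol article*

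**What the plan says.** The protocol article, under the relationship between time spent walking and outcome, sets the coding rule: "With the exception of pre-operative function and surgical procedure, all confounding variables will be dichotomised". Table 3 then fixes the cuts: age at 65 years, BMI at 30, PHQ-9 and GAD-7 at 10, and symptom duration at the sample median ("< median (months").

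The section on confounding variables gives the same cut-offs for the two mood scales: "Depression will be assessed using the Patient Health Questionnaire Depression Scale (PHQ-9), using a cut off score of ≥10" and "Anxiety will be scored using the Generalised Anxiety Disorder 7-item Scale (GAD-7), using a cut off score of ≥10". It also collapses the activity questionnaire ("the two categories of low and moderate/high activity levels will be used for data analysis") and the ODQ walking item ("Participants will be categorised as having limited mobility if they score 3 or more").

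The other entries in Table 3 differ in kind:
- Gender, smoking, diabetes, self-reported neurological deficit and single versus multi-level surgery are recorded with two levels.
- Surgical procedure keeps three levels.
- Baseline ODQ keeps five bands of about 20 points.
- Walking time, the exposure, stays in minutes.

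Table 1 shows that age, height, weight, PHQ-9, GAD-7 and duration of symptoms are all collected before surgery. The article describes no analysis that uses the numeric values of the five cut variables for adjustment.

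**The concern.** These variables are in the model to remove confounding from the walking odds ratio. A two-level term adjusts only for the difference between the two halves. A patient of 20 and one of 64 are treated as alike, while 64 and 65 are treated as different. If, within each half, older, heavier, more depressed or longer-suffering patients walk less and recover less well, that association stays in the walking coefficient and walking looks more beneficial than it is.

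This matters because of how the result is to be used. The Discussion attributes poorer outcome to limited walking and expects the findings to inform whether raising activity should be a rehabilitation target. Residual confounding in the direction just described would push towards that conclusion.

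**Working it through.** **1. The plan's own figure.** The recruitment and sample size section uses 5 events per variable and 15 variables. That is 5 × 15 = 75 events, and 75 / 0.50 = 150 participants. The stated minimum of 150 is reproduced, but only at an event share of 50%, which is implied and not stated.

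**2. What two-level coding keeps of one variable.** For a normal variable with a share *p* above the cut *z*, the fraction of variance kept is R² = φ(z)² / [p(1 − p)]. At the median, φ(0)² = 0.159 and 0.159 / 0.25 = 0.637. If *ρ* is the variable's correlation with walking, the share of its confounding that remains is (1 − R²) / (1 − ρ²R²), for linear effects.

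| Share above cut | Variance kept | Variance lost | Confounding left, ρ = 0.1 to 0.5 |
|---|---|---|---|
| 50% | 64% | 36% | 37% to 43% |
| 35% | 60% | 40% | 40% to 47% |
| 30% | 58% | 42% | 43% to 50% |
| 20% | 49% | 51% | 51% to 58% |
| 10% | 34% | 66% | 66% to 72% |

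The shares above the cut are assumptions, except that duration is split near 50% by construction. Large-sample logistic simulation (n = 400,000, one confounder, no walking effect) agrees: 38% to 42% left at a median split, 53% to 59% at 20% and 69% to 74% at 10%. Entering the variable as a linear term leaves about none.

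Skewed shapes were also tried. A skewed PHQ-9-like score cut at 10 loses about 33% of its variance. A lognormal duration split at its median loses 36% on the log scale and 73% on the raw scale.

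**3. Baseline ODQ.** With assumed means of 40 to 50 and SDs of 15 to 18, five bands keep 87% to 90% of the variance, so about 10% to 13% is lost.

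**4. The whole Table 3 set.** A simulation used seven cut variables (the five above, the activity category and the ODQ walking item), six two-level variables and ODQ in five bands. Every confounder worked in the same direction, worse-risk patients walked less, and walking had no true effect.

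| Assumed associations | Crude odds ratio per SD of walking | Planned coding | Share of crude confounding left |
|---|---|---|---|
| Weaker, three correlation patterns | 1.20 to 1.62 | 1.05 to 1.07 | 14% to 26% |
| Weaker, ODQ given triple weight | 1.62 | 1.09 | 17% |
| Stronger, three correlation patterns | 1.78 to 3.63 | 1.22 to 1.37 | 25% to 35% |

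Full numeric adjustment returned log odds ratios between −0.007 and 0.003, that is, essentially no bias.

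**5. Coefficients.** In Table 3, 13 variables take one coefficient each, procedure takes 2 and ODQ takes 4 if its bands are dummy coded: 13 + 2 + 4 = 19. At 5 events each this is 95 events, or 95 / 0.50 = 190 participants.
- Making the five cut variables linear leaves the count at 19.
- Making ODQ linear as well gives 19 − 3 = 16, or 80 events and 160 participants.
- Three-knot splines on the five variables, with ODQ still in bands, give 24, or 120 events and 240 participants.

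**The case against.** The strongest reply is that a reader of the coding rule might infer that every confounder is damaged and that a large share of all confounding goes unadjusted. The documents do not support that. Five of the twelve two-level confounders are two-level as recorded and lose nothing, procedure is not cut in two, and ODQ, plausibly a main confounder, keeps most of its information. Across the whole set, 14% to 35% of crude confounding was left under the assumptions shown. The losses of 36% or 51% apply to one variable at a time. This part of the reply stands.

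The size of the bias is also open. The scenarios above have all confounders acting in one direction. Milder settings at n = 200 (six confounders, one kept continuous, log odds ratio −0.2 per SD, correlation −0.1 with walking) gave odds ratios of only 1.04 to 1.06 and a type I error of 6% to 7%. Opposite-signed associations would pull the estimate below 1. A reader might want a definite false-positive rate, but the protocol gives nothing from which to fix one.

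It can also be said that the PHQ-9 and GAD-7 cuts are cited, that BMI of 30 is the usual meaning of obesity as a risk factor, and that the median rule is set in advance without reference to outcome. All true: none of the cuts is chosen to favour a result. A cited cut-off supports classifying patients, however. It does not show that risk is flat on either side of the cut, which is what two-level adjustment assumes. The overlap between the ODQ walking item and the ODQ total is already covered by the planned correlation check and adds nothing here.

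Finally, the sample size might seem to call for simple coding. It does not, because a linear term and a two-level term each cost one coefficient.

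**Conclusion.** The concern holds for five variables: age, BMI, PHQ-9, GAD-7 and symptom duration. With roughly normal scores and effects linear on the logit scale, two-level coding leaves about a third to a half or more of the confounding by each of them in the walking estimate. If a variable's true effect were a step exactly at the cut, nothing would be lost, but the article does not argue this.

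The consequence for the walking odds ratio cannot be determined from the documents. With no true effect and worse-risk patients walking less, assumed scenarios give about 1.05 to 1.2 or more per SD of walking. The figures assume that all Table 3 variables enter the model.

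This is a stated coding rule and not a detail left to a later plan. It should be changed because the improvement is free, whatever the exact size of the bias.

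**What to change.** In the data analysis section and Table 3:
- Enter age, BMI, PHQ-9, GAD-7 and log symptom duration as continuous linear terms. This costs no extra coefficients and needs no new data. If a duration of zero can occur, state how it is handled on the log scale.
- Enter baseline ODQ as a continuous term. This saves three coefficients if the bands were to be dummy coded. The article does not say whether they were, and if they were to enter as one ordered term the count is unchanged.
- Keep the Table 3 categories for describing the sample only, and leave the variables recorded with two levels as they are.
- Use a spline only where non-linearity is evident and the number of events allows. A three-knot spline adds one coefficient per variable. With ODQ linear, all five would bring the count to 16 + 5 = 21, which at 5 events each is 105 events, or 210 participants at an assumed 50% event share. That is inside the planned 250 before losses, with limited room if the event share is further from 50%.
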